### Data analysis plan

Data will be analyzed as intention to treat using univariate and multivariate methods in STATA version 13. PCM-IT scores will be compared using Student’s *t*-test and linear regression models will be used to control for confounders. Survival and other related outcomes in the four groups will be analyzed using Cox proportional hazards analysis. All estimates will be adjusted for cluster allocation according to generalized estimating equation method.

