## Methods/Design

### Objective and hypothesis

The primary aim of this study is to determine whether an integrated neonatal survival kit and/or newborn stimulation package, when delivered to pregnant women during their third trimester of pregnancy by volunteer CHWs, improves developmental outcomes at 12 months of age. Through a reduction in severe infections and improved thermoregulatory care in the first month of life, we hypothesize that utilization of the neonatal survival kit will result in an improvement of at least one standard deviation in development at 12 months of age as measured by the Protocol for Child Monitoring – Infant/Toddler version (PCM-IT) assessment. Moreover, we hypothesize that the combination of both the neonatal survival kit and early stimulation messaging will have an additive effect on development. Secondary objectives are: i) to determine if introduction of the neonatal survival kit reduces all-cause neonatal mortality; ii) explore whether use of the kit is effective in reducing the incidence of omphalitis and/or severe infection, improves caregiver ability to identify hypothermia and/or fever through use of ThermoSpot, and improves identification of low birth weight through use of a handheld scale. The study will also determine if the interventions increase appropriate referral to local health facilities. Finally, the study will assess knowledge, attitudes, and practices of mothers with their newborn and their willingness to use the kit and their capacity to pay for it.

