### Design and cluster definition

This community-based study is a cluster randomized controlled, pragmatic, open label intervention trial with four trial arms: neonatal survival kit; stimulation messaging; combination of neonatal survival kit with stimulation messaging; and control (current standard of care in Kwale County [38]) (Fig. 2). A cluster is defined as a single CHW, where each CHW is responsible for the provision of basic health promotion and disease prevention services to approximately 20 households. Within one village, the distance between homes covered by one CHW can be large. Geographic distance thus minimizes any unintended diffusion of arms of interventions between households, especially those serviced by different CHWs (clusters).

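### For four arms that form a 2×2 layout, the plan names only a two-group t-test for PCM-IT, so no stated contrast estimates the hypothesised additivity or uses all infants for the kit effect

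*Protocol article*

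**What the plan says.** All places are in the protocol article.

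- *Design and cluster definition* lists the arms as "neonatal survival kit; stimulation messaging; combination of neonatal survival kit with stimulation messaging; and control". The word factorial is not used, but this is kit yes/no crossed with stimulation yes/no. The same section fixes the unit: "A cluster is defined as a single CHW".
- *Objective and hypothesis* expects a kit effect of at least one standard deviation on PCM-IT and adds that "the combination of both the neonatal survival kit and early stimulation messaging will have an additive effect on development". A secondary objective is "to determine if introduction of the neonatal survival kit reduces all-cause neonatal mortality".
- *Sample size and power estimation* claims more than 90 % power for 1 SD on PCM-IT and more than 80 % for a 40 % mortality reduction, for a comparison of whichever two arms are chosen.
- *Data analysis plan* says "PCM-IT scores will be compared using Student’s *t*-test", and the same sentence adds linear regression for confounder control. Mortality in the four groups goes to Cox regression. The section closes with "All estimates will be adjusted for cluster allocation according to generalized estimating equation method".

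**The concern.** The hypotheses and the named test do not match. Additivity says that adding stimulation to the kit brings as much as adding stimulation to nothing. That is a statement about four arm means. A t-test compares two, and regression is mentioned only for confounders, so nothing named in the section answers the hypothesis.

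The kit questions are put as the effect of the kit. Two of the four arms receive the kit and two do not. A comparison of one kit arm with one non-kit arm sets aside the other two arms, which is half the infants.

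Lastly, a Student's t-test treats children as independent, whereas the closing sentence promises GEE for every estimate. Both cannot describe the same primary result, so it is unclear which number will be reported.

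At stake are an unanswered hypothesis, avoidable imprecision (chiefly for mortality, where events are few) and a choice of contrast that could be made after the data are seen.

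**Working it through.** **Inputs from the article.** 689 clusters; about 5 live births per cluster; 90 % enrolment; up to 10 % loss; baseline neonatal mortality 44 per 1000; 40 % reduction, hence 44 × 0.6 = 26.4 per 1000. PCM-IT is measured in a subset of unstated size.

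**Assumptions.** Two-sided 5 %; no clustering; no interaction where arms are pooled. For mortality, stimulation itself is taken to have no effect.

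**Sample per arm.** 689 × 5 × 0.9 × 0.9 = 2790 infants; 2790 / 4 ≈ 698.

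**The plan's own figures first.**

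- PCM-IT, 1 SD, two arms: 22 per arm gives 1/√(2/22) = 3.32, and Φ(3.32 − 1.96) ≈ 91 %. The claim of more than 90 % is reproduced as a lower bound, and holds for any subset of at least about 22 per arm, ignoring clustering.
- Mortality, two arms: SE = √[(0.044 × 0.956 + 0.0264 × 0.9736)/698] = 0.00985; 0.0176/0.00985 = 1.79; Φ(1.79 − 1.96) ≈ 43 %. The claim of more than 80 % is not reproduced. It would need about 1720 per arm.

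**Contrasts on PCM-IT.** Let n be the number assessed per arm, in SD units.

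- Two arms, e.g. kit − control: SE = √(2/n).
- Kit main effect, (kit + both)/2 − (stimulation + control)/2: SE = √(4 × ¼ × 1/n) = √(1/n).
- Interaction, (both − kit) − (stimulation − control): SE = √(4/n).

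Main effect against two arms: √(1/n)/√(2/n) = 0.71, a 29 % smaller SE at any equal n per arm. The difference detectable with 80 % power is 2.80 × SE:

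| n per arm | two arms | main effect | interaction |
|---|---|---|---|
| 100 (illustrative) | 0.40 SD | 0.28 SD | 0.56 SD |
| 698 (every child assessed) | 0.15 SD | 0.11 SD | 0.21 SD |

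At 698 the three SEs are 0.054, 0.038 and 0.076 SD.

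**Mortality, kit against no kit.** With 2 × 698 per side, SE = 0.00985/√2 = 0.00697; 0.0176/0.00697 = 2.53; Φ(2.53 − 1.96) ≈ 71 %. A Schoenfeld calculation, closer to the planned Cox model, agrees: 698 × (0.044 + 0.0264) ≈ 49 deaths give 43 %, and twice that, 98 deaths, gives 72 %.

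**Precision of a mortality interaction.** Expected deaths are 698 × 0.044 ≈ 30.7 in each non-kit arm and 698 × 0.0264 ≈ 18.4 in each kit arm. The SE of the log ratio of hazard ratios is about √(2/30.7 + 2/18.4) = 0.42, so the 95 % interval reaches a factor of exp(1.96 × 0.42) ≈ 2.3 either way.

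**The case against.** **A reader might infer that clustering is ignored.** The article does not support that. Its analysis section applies GEE to all estimates, and a comparison of two means is a linear model with an arm indicator, whose cluster-adjusted form is an identity-link GEE. A t-test reported without adjustment would have a type I error of 5.7 %, 6.8 % or 8.6 % at an assumed ICC of 0.02, 0.05 or 0.10. This uses a design effect of 1 + (4.05 − 1) × ICC, with 2790/689 = 4.05 children per CHW. Those errors arise only if the article's own sentence is not followed, and they shrink if the subset has fewer children per CHW. What stands is a mismatch of wording.

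**A reader might infer that additivity cannot be tested.** That is also too strong. Linear regression and GEE are both in the plan, either can carry a kit × stimulation term, and an analysis plan not shown may specify one. The hypothesis can also be read as the combination beating each intervention alone, which pairwise contrasts do address. What stands is that the article fixes a two-group test and pairwise power, and gives no model the task of estimating additivity.

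**A reader might infer that half the data are wasted.** Arm-by-arm comparison is a legitimate multi-arm choice and stays valid under interaction. The main effect is a different quantity, the kit effect averaged over stimulation, and its gain is clean only if interaction is small. This is a fair reason not to replace the pairwise comparisons. It is a weaker reason to omit the pooled estimate, because the protocol itself expects additivity.

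**Conclusion.** The point holds in a limited form. The only comparison named for PCM-IT is a two-group test, while the trial's own hypothesis needs a four-arm contrast and its kit questions can draw on all four arms.

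For PCM-IT the gain is a 29 % smaller SE for a kit effect, given equal numbers per arm and little interaction. The absolute SEs depend on the unstated subset size. The stated power for 1 SD does not depend on this choice. For mortality, power rises from about 43 % to about 71 % under the assumptions listed in the working. The pooled figure is still short of the more than 80 % claimed for a pair of arms, and clustering would lower both. The GEE sentence shows that cluster adjustment is intended, and only the t-test wording conflicts with it.

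This is a worthwhile correction to the analysis wording. It does not make the trial's main comparison invalid.

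**What to change.** 1. Replace the Student's t-test with an identity-link GEE linear model for PCM-IT, clustered on CHW, with robust standard errors. Keep the estimates of each arm against control from this model.
2. Add a prespecified model with kit and stimulation main effects and their interaction. Report the interaction with its 95 % CI as the test of additivity. Additivity means an interaction of zero, so the width of the interval matters more than a non-significant p-value.
3. Use the same structure for neonatal mortality: kit against no kit pooled over stimulation, the interaction, and each arm against control.
4. State before unblinded analysis which of these estimates carries the primary claim.

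The cost is analysis-plan wording, with no extra participants or data. The drawback is that main effects are hard to interpret if the interaction is large, so the arm-level estimates must always stand beside them. For mortality the interaction will be imprecise and can rule out only large departures from a common kit effect.

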## Discussion

Awareness of the importance of child development is increasing in LMICs. Interventions that aim to promote early child development alongside the prevention and timely detection of newborn illness are important investments in minimizing the loss of human capital [35]. While evidence exists in support of various interventions and delivery mechanisms to promote child development, at present, very few studies have explored the feasibility and effectiveness of volunteer community health workers delivering interventions that aim to promote development and/or reduce newborn morbidity and mortality directly to women during pregnancy. The utilization of CHWs to deliver and provide education regarding the interventions has the potential to positively influence the health of the community and will facilitate national scale-up and long-term sustainability. Indeed, the effectiveness of CHWs in delivering key health promotion messages has been previously demonstrated [48]. The findings of this trial will provide evidence to inform policy on the implementation of sustainable interventions in rural settings to promote child development and reduce risk factors of compromised development, newborn morbidity and mortality.

### Trial status

Enrolment in ongoing

## Abbreviations

CHEW: Community health extension worker
CHS: Community health strategy
CHW: Community health worker
DMC: Developmental milestones checklist
DMU: Data management unit
ECD: Early childhood development
KDHS: Kenya demographic and health survey
KDI: Kilifi developmental inventory
KMC: Kangaroo mother care
LBW: Low birth weight
LMIC: Low and middle income country
MDG4: Millennium development goal 4
PCM-IT: Protocol for child monitoring – infant and toddler version
PSED: Profile for socio-emotional development
